**After the first 100 subjects enrolled:**

- - 8% or more participants who received at least one study injection to date experience severe (Grade 3/4) study injection-related local reaction of the same category other than measured erythema or induration.
  - 4% or more participants who received at least one study injection to date experience a severe (Grade 3/4) study injection-related systemic reaction of the same category (excluding laboratory AEs, which will be monitored separately).
  - 2% or more participants who received at least one study injection to date experience a severe (Grade 3/4) study injection-related abnormality in the same laboratory parameter.

These halting rules refer to adverse reactions suspected to be vaccine related.

Butantan retains the right to temporarily suspend or prematurely discontinue this study at any time related to safety. If the study is stopped or suspended prematurely, Butantan will inform the local principal investigator as well as regulatory authorities about the decision and the reasons for termination or suspension. If such action is taken, all efforts must be made to ensure the safety of the participants enrolled in the study. The principal investigator will assist Butantan in informing the responsible IRB/ethics committee and provide the reason for the suspension or termination. In case of premature study or study clinic closure, the monitor will conduct all activities as indicated in the Clinical Monitoring Plan.

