**Table 5 Classification of the severity of the laboratory adverse events.**

| **Adverse event** | **Grade 1** | **Grade 2** | **Grade 3** | **Grade 4** |
| --- | --- | --- | --- | --- |
| Hemoglobin decrease compared to baseline - gm/dL | 0.1 – 1.5 | 1.6 – 2.0 | 2.1 – 5.0 | >5.0 |
| Hemoglobin (women) - gm/dL | 11.0 – 12.0* | 9.5 – 10.9 | 8.0 – 9.4 | <8.0 |
| Hemoglobin (men) - gm/dL | 12.5 – 13.5* | 10.5 – 12.4 | 8.5 – 10.4 | <8.5 |
| Leukocytosis – cell/mm3 | 10,800^†^– 15,000 | 15,001 – 20,000 | 20,001 – 25,000 | >25,000 |
| Leukopenia – cell/mm3 | 2,500 – 3,500* | 1,500 – 2,499 | 1,000 – 1,499 | <1,000 |
| Lymphopenia – cell/mm3 | 750 – 1,000* | 500 – 749 | 250 – 499 | <250 |
| Neutropenia – cell/mm3 | 1,000 – 1,499* | 500 – 999 | 300-499 | <300 |
| Platelets Decreased – cell/mm3 | 125,000 – 140,000* | 100,000 – 124,000 | 25,000 – 99,000 | <25,000 |
| Creatinine – mg/dL | 1.5^†^ – 1.7 | 1.8 – 2.0 | 2.1 – 2.5 | >2.5 or requires dialysis |
| ALT/AST – increase by factor | 1.1 – 2.5 x ULN | 2.6 – 5.0 x ULN | 5.1 – 10 x ULN | >10 x ULN |
| Bilirubin – when accompanied by any increase in ALT/AST – increase by factor | 1.1 – 1.25 x ULN | 1.26 – 1.5 x ULN | 1.51 – 1.75 x ULN | >1.75 x ULN |
| Bilirubin – when ALT/AST are normal – increase by factor | 1.1 – 1.5 x ULN | 1.6 – 2.0 x ULN | 2.0 – 3.0 x ULN | >3.0 x ULN |

ILN: inferior limit of the normal range.

ULN: upper limit of the normal range.

* If the ILN is less than the upper limit of Grade 1, the ILN will be used as an upper limit to Grade 1.

^†^ If the ULN is greater than the lower limit to Grade 1, the ULN will be used as a lower limit to Grade 1.

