### 9.3.8 Procedures for Out-of-range Laboratory Test Values

Out-of-range laboratory values and AEs. To the extent possible, all reference ranges for clinical laboratory test results will be pre-specified. The site staff will follow the Toxicity Table (Table 5). Laboratory values that are out-of-range will not be considered an AE unless they qualify as a Grade 2 or above on the Toxicity Table. The reference ranges for the laboratory will be taken in to consideration when determining out of range results.

Out-of-range test values may be considered an SAE if two circumstances are met:

1. the value rises to the level of Potentially Life-threatening (Grade 4), and
2. the event is determined by the Principal Investigator to pose an immediate risk of death.

A Grade 4 laboratory result does not, in and of itself, constitute an SAE. Grade 4 places a laboratory value as a potentially life-threatening event, but a Grade 4 laboratory result should not be reported as an SAE unless the PI has determined that it does, in fact, pose an immediate risk of death.

Assessing relatedness and clinical significance of out-of-range laboratory values: All laboratory results should be reviewedAny laboratory finding Grade 2 and above is regarded as an AE. The investigator will assess relatedness and clinical significance for these findings.

Clinical judgment always should be used to determine whether a laboratory result requires additional follow up. However, the investigator should redraw any Grade 2 or above laboratory result that is deemed clinically significant at an unscheduled visit to check if the result has normalized.

Any Grade 2 or above laboratory value that is clinically significant and has not returned to normal or stabilized by day V2+194 should be marked by the investigators as “continuing” or “unresolved.” The investigator should assure that the participant is referred for appropriate medical follow-up, if indicated.

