## 9.6 Halting Rules

Study enrollment and dosing will be halted and an ad hoc DSMB review/recommendation will be performed if any of the following occur:

Study Halting Events:

1. One or more participant experiences ulceration, abscess, or necrosis at the site of injection associated with product administration.
2. One or more participant experiences laryngospasm, bronchospasm, or anaphylaxis within 24 hours following administration of study product that is associated with product administration.
3. One or more participant experiences a study injection related SAE (excluding laboratory related SAEs, which will be managed as described in section 9.3.8).

1. Two or more participants experience generalized urticaria within 72 hours that is associated with product administration.
2. During the 7 days after each study injection, any of the following occurs across all treatment groups:

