**For the first 100 subjects:**

- - Five or more participants who received at least one study injection to date experience severe (Grade 3/4) study injection-related local reaction of the same category other than measured erythema or induration.
  - Three or more participants who received at least one study injection to date experience a severe (Grade 3/4) study injection-related systemic reaction of the same category (excluding laboratory AEs, which will be monitored separately).
  - Three or more participants who received at least one study injection to date experience a severe (Grade 3) study injection-related abnormality in the same laboratory parameter.
  - Two or more participants who received at least one study injection to date experience a severe (Grade 4) study injection-related abnormality in the same laboratory parameter.

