### 9.7.2 Data Safety and Monitoring Board (DSMB)

Safety monitoring will be closely conducted by a Data Safety and Monitoring Board (DSMB). The DSMB is appointed by but external to Butantan and is comprised of an independent group of experts with experience in clinical research studies. The primary responsibility of the DSMB is to monitor participant safety. DSMB activities will be delineated in the DSMB charter. The DSMB meets regularly throughout the study and on an ad hoc basis when required.

The DSMB will have access to unblinded data during its closed session(s), if applicable. After its assessment, they will recommend continuation, modification, or termination of the clinical trial.

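### After participant 100, section 9.6 drops its separate halt for two related Grade 4 results in one laboratory parameter; only a pooled 2% Grade 3/4 limit remains

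*Protocol*

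**What the plan says.** Protocol 9.6 gives the consequence of meeting any rule: "Study enrollment and dosing will be halted and an ad hoc DSMB review/recommendation will be performed". The reactogenicity and laboratory limits concern the 7 days after each injection and apply if "any of the following occurs across all treatment groups".

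- **First 100 subjects.** There are two laboratory limits, each for related results in the same parameter: three or more participants with Grade 3, and separately "Two or more participants who received at least one study injection to date experience a severe (Grade 4) study injection-related abnormality".
- **After the first 100.** There is one laboratory limit: "2% or more participants who received at least one study injection to date experience a severe (Grade 3/4) study injection-related abnormality", again in the same parameter.

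Item 3 of the same section halts on a single related SAE, but with the qualification "excluding laboratory related SAEs, which will be managed as described in section 9.3.8". Section 9.3.8 contains no halting rule and states: "A Grade 4 laboratory result does not, in and of itself, constitute an SAE".

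**The concern.** Grade 4 is the highest laboratory grade in the protocol. Early on, two related cases in one parameter are enough to stop and call the DSMB. Later the number required is a percentage of everyone injected, active arms and placebo together, with Grade 3 and Grade 4 counted as one. A cluster of Grade 4 results in one of eight arms is diluted by the other seven. The local and systemic limits already merge Grades 3 and 4 before participant 100, so only the laboratory limits change structure at the switch. The protocol gives no reason for the change.

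At stake is whether a small cluster of very abnormal values in one formulation stops dosing automatically, or depends on someone noticing it and choosing to act.

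**Working it through.** **Inputs from the protocol.** N = 432 in 8 arms of 54 (Table 3, 11.1); the limits in 9.6. The protocol states neither case counts for the 2% limit nor any halting probability, so there is no figure of its own to reproduce.

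**Step 1: the limit as a count.** The smallest whole number at or above 2% of n is ceil(0.02 × n).

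| Injected to date | Grade 3/4 cases needed |
|---|---|
| 100 | 2 |
| 101–150 | 3 |
| 151–200 | 4 |
| 201–250 | 5 |
| 251–300 | 6 |
| 301–350 | 7 |
| 351–400 | 8 |
| 401–432 | 9 |

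At n=100 the percentage equals the earlier Grade 4 count of two. For Grade 3 the switch does not loosen anything: 3 before, 3 at n=101. With no Grade 3 in the parameter, eight Grade 4 cases at n=432 (8/432 = 1.85%) do not meet the limit. If all eight were in one arm, that is 8/54 = 14.8% of the arm.

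**Step 2: other automatic rules.** Item 3 excludes laboratory SAEs and sends them to 9.3.8, which has no halt. If the first-100 rule is read as following that cohort through its second dose, it still leaves out 432 − 100 = 332 participants (332/432 = 77%).

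**Step 3: how often each rule fires.** The protocol gives no Grade 3 or Grade 4 rates, so all rates here are assumptions. The simulation uses permuted blocks of 8, one laboratory parameter, and one outcome per participant (Grade 4, Grade 3 or neither) in one arm, with no events elsewhere. Trials with two or more Grade 4 or three or more Grade 3 in the first 100 count as already halted and are removed. In the rest, the written limit fires if the combined count reaches ceil(0.02n) at any n from 101 to 432. The continued rule fires if the cumulative Grade 4 count reaches two.

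Results at 5% Grade 4 in the affected arm:

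| Grade 3 in that arm | 2% limit | Two Grade 4, continued | Either | Added by the continued rule |
|---|---|---|---|---|
| 0% | 3% | 72% | 72% | 70 points |
| 5% | 30% | 73% | 76% | 46 points |
| 10% | 65% | 73% | 85% | 20 points |
| 15% | 87% | 73% | 93% | 6 points |

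By n=250 the continued rule has fired in about 39% of trials, so much of the 72% comes late in enrollment.

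At 2% Grade 4 the continued rule fires in about 28%. The 2% limit fires in under 1%, 14% or 46% with 0%, 5% or 10% Grade 3.

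**Step 4: unnecessary halts.** Let q be an assumed background rate of Grade 4 results judged related, per participant and parameter. The chance per parameter is p = P(Bin(432, q) ≥ 2). Over about ten Table 5 parameters, taken as independent, it is 1 − (1 − p)^10.

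| q | Per parameter | Over ten |
|---|---|---|
| 0.01% | 0.1% | 1% |
| 0.02% | 0.4% | 3% |
| 0.05% | 2% | 18% |
| 0.1% | 7% | 52% |

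**The case against.** The strongest reply is that this is an ordinary move from counts to rates. All three reaction limits become percentages after 100 subjects, and 2% of 100 is exactly two. A fixed count of two becomes stricter as exposure grows: 2/432 is 0.46%. The merged limit also catches mixtures that the early rules miss. Two Grade 3 plus one Grade 4 does not halt within the first 100 but does at n=101–150. This stands, and it means the protocol has not abandoned its tolerated rate. It does not settle the matter, because 9.6 already uses fixed counts at any n for rare, serious events: one related SAE, two cases of generalized urticaria. An isolated related Grade 4 laboratory result fits that group.

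A reader might infer that Grade 4 laboratory toxicity goes unmonitored after participant 100. The protocol does not support that. On the board it says: "The DSMB meets regularly throughout the study and on an ad hoc basis when required". The DSMB can see data by group (5.4.2) and formally reviews the S1 safety data of the first 100 participants (11.6). The safety physician reviews events (9.7.1), and an arm can be suspended at discretion (7.6.2). A related clinical SAE still halts the trial under item 3.

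A reader might also infer that nine Grade 4 cases are always needed late in the trial. That is true only if the parameter has no Grade 3 results, and graded continuous values will often produce some.

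The cost objection stands in part. A halt stops dosing, and the second dose has only a +7-day window (Table 1). The right count depends on a background rate that the protocol does not give.

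**Conclusion.** The point holds as a gap in the automatic trigger, and only there. After participant 100 no preset rule responds to a small cluster of isolated related Grade 4 values in one parameter unless Grade 3 and 4 together reach 2% of all participants injected.

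At an assumed 5% Grade 4 in one arm, continuing the two-participant rule adds about 70 points of detection with no Grade 3, and about 6 points when Grade 3 is near 15%. The 72% is the figure by the end of enrollment, not an early-warning probability. The text comparison and the counts are certain. The detection and false-halt figures rest on assumed rates, a single affected arm and independent parameters. This is a cheap improvement to a workable rule and does not make the trial's safety oversight inadequate.

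**What to change.** In 9.6, in the list for after the first 100 subjects, keep the 2% limit and add the existing Grade 4 rule beside it, with its same-parameter condition: "Two or more participants who received at least one study injection to date experience a severe (Grade 4) study injection-related abnormality". Nothing else in 9.6 needs to change. The local and systemic limits remain a judgement for the sponsor and DSMB.

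The edit is one line. The running cost is the occasional extra halt shown in step 4: about 1% to 3% of trials if background related Grade 4 results are very rare (0.01% to 0.02%), 18% at 0.05% and 52% at 0.1%. Each halt lasts until the DSMB has given its recommendation and may push some second doses past their window, so the DSMB should be ready to convene quickly.

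If the sponsor expects a background near 0.1%, a fixed count of three cuts unnecessary halts to about 1% per parameter (9% over ten). It would still fire in about 45% of trials at 5% Grade 4 in one arm.

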## 9.7 Safety Oversight

### 9.7.1 Study Safety Physician

The Study Safety Physician is a physician employed by Butantan with relevant expertise whose primary responsibility is to provide independent safety monitoring in a timely fashion. He/She will review SAEs and other AEs as needed and provide an independent assessment to the DSMB.

### 9.7.2 Data Safety and Monitoring Board (DSMB)

Safety monitoring will be closely conducted by a Data Safety and Monitoring Board (DSMB). The DSMB is appointed by but external to Butantan and is comprised of an independent group of experts with experience in clinical research studies. The primary responsibility of the DSMB is to monitor participant safety. DSMB activities will be delineated in the DSMB charter. The DSMB meets regularly throughout the study and on an ad hoc basis when required.

The DSMB will have access to unblinded data during its closed session(s), if applicable. After its assessment, they will recommend continuation, modification, or termination of the clinical trial.

# Clinical Monitoring

## 10.1 Monitoring Plan

Individuals qualified by education, training and experience will carefully monitor the study sites to ensure that the ICH/GCP guidelines are being followed. The study monitors will periodically contact the site and perform on-site visits. The extent, nature, and frequency of site visits will be based on such considerations as study objectives, study design and complexity, and enrollment rate; periodicity and nature of monitoring activities will be described in the Monitoring Plan*.* The Monitoring Plan will detail reporting requirements to Butantan to keep it apprised of study progress. Representatives of Butantan or its designees may participate in monitoring visits or visit the study clinic on its own to provide proper oversight.

# Statistical Considerations

## 11.1 Sample size

The sample size for this study is approximately 432 subjects, randomized equally into 8 treatment groups of approximately 54 subjects each. This sample size is consistent with previous phase 1 studies involving influenza vaccination, and is considered to be sufficient to evaluate preliminary safety and dose-ranging immunogenicity.

Power calcultations for the detection of adverse events by study arms are described in Table 8.

- In each of the active arms (N = 54), there is a 94% power to detect an event with frequency ≥ 5%.
- For all combined dose levels of vaccine adjuvanted with IB160 (N = 162) or SE (N = 162) there is a 80% power to detect an event with frequency ≥ 1%.

**Table 8. Safety – Statistical Power for Detecting at Least 1 Safety Event Based on a Range of True Event Rates**

| **True Event Rate (%)** | **N = 54** | **N = 162** |
| --- | --- | --- |
| 0.1 | 5% | 15% |
| 0.5 | 24% | 55% |
| 1 | 42% | 80% |
| 2 | 66% | 96% |
| 3 | 81% | 99% |
| 4 | 89% | >99% |
| 5 | 94% | >99% |

Sample size and statistical power were determined using PASS® v. 15.0.2. Calculations can be checked using the following binomial distribution formula: Power (%) = (1-(1-taxa real de evento)^N). Considering true real rate of event = 0.5% and N=54, Power (5) = 100*(1-(1-0.005)^54)=23.7% turning to 24%.

## 11.2 Data Analysis

The planned statistical analyses for this study are outlined below. A detailed statistical analysis plan for preparation of the final study report will be created and made final prior to database lock and unblinding. Butantan and IDRI will participate in the review and approval of the statistical analysis plan.

Antibody titers will be transformed into log10 for the calculation of their geometric mean, and mean geometric increase. Adverse events will have their individual percentages calculated for each intervention group. Results will be summarized by point estimates, and respective 95% confidence intervals (CI). Exact (Clopper-Pearson) CIs will be calculated for all proportional endpoints. The distribution of HI antibody titers from each intervention group will be described by reverse cumulative distribution curves.

## 11.3 Definition of Analysis Sets

Definitions of populations to be analyzed are:

Enrolled Population

All screened participants who provide informed consent, regardless of the participant’s randomization and treatment status in the trial.

Full Analysis (FA) Population

All participants in the enrolled population who were randomized and received a study vaccination. This population will serve as the primary analysis population for all safety objectives and may serve also in secondary immunogenicity analysis. The analysis based on this population will serve as the supportive results for all safety objectives. Participants will be analyzed as received..

Per Protocol (PP) population

All participants in the Full Analysis population who have valid post vaccination immunogenicity measures with no major protocol deviations that are determined to potentially interfere with the immunogenicity assessment of the study vaccine. This population will serve as the primary analysis population for all immunogenicity objectives.

The criteria for exclusion of participants from the Per Protocol Population will be established before breaking the blind and will be based on the blinded review of major protocol deviations.

## 11.4 Analysis of Immunogenicity Endpoints

Immune responses to the vacccine will be evaluated by the following:

- the number of participants with a serum HI antibody titer ≥ 1:40 post-vaccination measured on days V1+28, (+7d), V2+7 (+3d) e V2+28 (+7d);;
- the number of seroconverted participants; that is with a serum HI titer on days V1+28, (+7d), V2+7 (+3d) e V2+28 (+7d);meeting the following criteria:
  - pre-vaccination titer <1:10 and a post-vaccination titer ≥ 1:40 or
  - pre-vaccination titer ≥ 1:10 and at least a four-fold increase in post-vaccination measured.
- the geometric mean titers (GMTs) of Serum Hemagglutination Inhibition (HI) antibodies pre- (V1) and post-vaccination (V1+2, (+7d), V2+7 (+3d) e V2+28 (+7d);
- the geometric mean fold rises (GMFRs) of Serum Hemagglutination Inhibition (HI) antibodies (post-vaccination / pre-vaccination).
- the number of participants with a serum MNT antibody titer ≥ 1:40 post-vaccination measured on day V1+28 and V2+28 (+7d);
- the number of seroconverted participants; that is with a serum MNT titer on day V1+28 and V2+28 (+7d); meeting the following criteria:
  - pre-vaccination titer <1:10 and a post-vaccination titer ≥ 1:40 or
  - pre-vaccination titer ≥ 1:10 and at least a four-fold increase in post-vaccination measured.
- the geometric mean titers (GMTs) of MNT antibodies pre- (V1) and post-vaccination V1+28 and V2+28 (+7d);
- the geometric mean fold rises (GMFRs) of MNT antibodies (post-vaccination / pre-vaccination).

Percentages of participants with immune response will be calculated along the corresponding two-sided exact CIs. GMT will be summarized by treatment group along with the corresponding two-sided 95% CIs, by exponentiating the corresponding log-transformed means and their 95% CIs. Titers below the lowest limit of quantitation (i.e. below the starting dilution of assay reported as “< 10”) will be set to half that limit (i.e. 10/ 2 = 5). If a titer is reported as greater or equal to the upper limit of the assay, it will be set to that limit.

## 11.5 Analysis of Safety Endpoints:

The safety profiles will be evaluated by the proportion of subjects experiencing AEs, related or not related, of the following four categories:

- Immediate reactions occurring within 30 minutes of administration of any dose, measured as observed by study staff or reported by the subject to study staff.
- Adverse events (reactogenicity) commonly associated with intramuscular vaccination (solicited local and systemic reactions) occurring through 7 days following any dose, measured as observed by study staff or reported by the subject to study staff.
- All other adverse events (including unsolicited events) following any dose, measured as observed by study staff or reported by the subject to study staff over the entire study period. This includes clinical findings and abnormal laboratory findings from blood specimens collected on Days 7 and 35.
- All serious adverse events (SAEs) occurring throughout the study period, as observed by study staff, reported by the subject to study staff, or noted by the subject diary card. This includes clinical findings and Grade 4 abnormal laboratory findings from blood specimens collected on Days 7 and 35 considered as life threatening.
- All adverse events of special interest (AESIs) occurring throughout the study period, as observed by study staff, reported by the subject to study staff, or noted by the subject diary card. This includes clinical findings and Grade 4 abnormal laboratory findings from blood specimens collected on Days 7 and 35 considered as life threatening.

Counts of all events will be reported and summarized according to event severity, as “any local AE”, or “any systemic AE”, and by relationship to administration of study product, as deemed by a blinded study clinician. Percentages of subjects experiencing each reaction or event, or at least one reaction or event will be calculated along with two-sided exact 95%CIs.

